##### Exclusion criteria

2.2.1.1

Only workers unwilling or unable to complete the assessments will be excluded.

Criteria of follow-up match the criteria for referral to a cardiovascular risk appointment by the Occupational Health physician. These criteria will be based on the Cardiovascular Prevention recommendations from 2021 of the European Society of Cardiology (ESC) and are as described in Table 1, regardless of whether there is a previous history of atherosclerotic disease. The combined use of the SCORE2 and SCORE algorithms reflects data availability in the OM setting: in the case of unavailability of HDL-cholesterol in the OM setting, the legacy SCORE algorithm is used as a pragmatic fallback, consistent with the flexibility allowed under the 2021 ESC guidelines (4, 11, 12).

**Table 1 T1:** Criteria for referral to a cardiovascular risk appointment by the occupational health physician, based on the cardiovascular prevention recommendations from 2021 of the European Society of Cardiology (ESC).

*Markedly elevated single risk factor*
• Total cholesterol >310 mg/dL or LDL cholesterol >190 mg/dL
• Blood pressure >180/110 mmHg
• Moderate or severe chronic kidney disease, defined as eGFR <60 mL/min/1.73 m^2^ (CKD-EPI 2021 creatinine equation)

** *Or very-high risk under SCORE2 stratification system* **
• SCORE2 ≥ 7.5% if < 50y or SCORE2 ≥ 10% if 50−69y (18).

** *Or high risk or very-high risk under SCORE stratification system* **
• SCORE 5%–9.9%(high-risk); ≥10% (very high risk) (11).

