### Study design and setting

2.2

Prospective pilot project for the integration of services, with a pragmatic design. Data collection lasts for 18 months in two distinct phases (Figure 1):
A cross-sectional 6-month intervention phase to enroll patients and operationalize the primary objective and secondary objectives 1, 2 and 5. This is to implement a process to promote the access to cardiovascular risk hospital appointments, through the systematic identification of very high CV risk patients in appointments from Occupational Health carried out on workers from the industrial/manufacturing companies of the municipality of São João da Madeira.A longitudinal, clinical follow-up phase, lasting 12 months, to assess secondary objectives 3 through 6. This is to estimate pharmacological therapy adherence and the impact on cardiovascular risk profile after the intervention above mentioned.

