**Figure 1 F1:**
[figure not shown]
Overview of patient participation and data collection. OM: Occupational Medicine; CV: cardiovascular; T0: first hospital consultation; T12: 12-month hospital consultation; a) CV risk consultation and/or Smoking cessation consultation, when applicable; b) Risk prediction algorithms: SCORE2 for patients aged 40 years or more with HDL available; SCORE for patients aged 40 years or more without HDL available; c) Risk prediction algorithms: SCORE2 for patients aged 40 years or more. The enrollment phase includes the OM consultations occurring in the identified companies. The follow-up phase includes the hospital appointments occurring in ULSEDV.

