#### Statistical methods

2.3.1

To address the multifaceted endpoints of this study (Table 3), a combination of statistical techniques will be employed. Descriptive statistics will be calculated to assess various CV risk factors. Continuous variables will be summarized using n, mean, median, standard deviation, minimum, maximum and 25th and 75th percentiles. Categorical variables will be summarized using frequency counts and percentages. Missing data will be reported using frequency counts and percentages and assessed for pattern and extent; where data are judged to be missing at random, multiple imputation will be used as the primary approach. Outliers will be identified using standard distributional criteria, and treated in consideration of their impact on the analysis.

**Table 3 T3:** Cardiogap + endpoints.

Endpoint Description
1. Proportion (%) of patients who meet the follow-up criteria for CV risk hospital consultation identified in OM consultation: Descriptive statistics will be used to calculate the percentage of patients who meet the follow-up criteria for CV risk hospital consultation over all patients attending OM consultations.
2. Proportion (%) of High CV risk individuals identified in OM consultation: Descriptive statistics will be used to calculate the percentage of High CV patients over all patients attending OM consultations.
3. Proportion (%) of Very High CV risk individuals identified in OM consultation: Descriptive statistics will be used to calculate the percentage of Very High CV patients over all patients attending OM consultations.
4. Proportion (%) of patients referred to Hospital CV Risk Consultation, overall and stratified by risk category: Descriptive statistics will be used to calculate the percentage of patients referred to Hospital CV Risk Consultation, reported (a) over allpatients meeting follow-up criteria, (b) over High CV risk patients only, and (c) over Very High CV risk patients only, identified in OM consultation.
5. Proportion (%) of Hospital CV Risk Consultation Participation after Referral by OM: Descriptive statistics will be used to calculate the percentage of individuals referred from OM consultations who participate in hospital CV risk consultations over all patients referred to hospital consultations.

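### Table 1 refers high-risk workers under SCORE but only very-high-risk workers under SCORE2, so endpoint 1 depends on HDL availability, and endpoint 2 or 4(b) misleads depending on how High is read

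*Protocol article*

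**What the plan says.** Section 2.2.1.1 makes the follow-up criteria identical to the referral criteria in Table 1. Apart from single markedly elevated factors (cholesterol, blood pressure, kidney disease), Table 1 has two score-based branches:

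- **HDL available:** "Or very-high risk under SCORE2 stratification system", with cut-offs beginning "SCORE2 ≥ 7.5% if < 50y" and a second one for ages 50 to 69. No SCORE2 band is printed for high risk.
- **HDL not available:** "Or high risk or very-high risk under SCORE stratification system", with the bands "SCORE 5%–9.9%(high-risk); ≥10% (very high risk").

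HDL availability alone selects the branch. Section 2.2.1.1 says that "in the case of unavailability of HDL-cholesterol in the OM setting, the legacy SCORE algorithm is used as a pragmatic fallback", and the Figure 1 legend assigns "SCORE for patients aged 40 years or more without HDL available".

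In Table 3, endpoint 1 is the share of all OM attendees who meet the follow-up criteria. Endpoints 2 and 3 are the shares at High and at Very High risk. Endpoint 4 is the share referred, taken (a) over everyone meeting the follow-up criteria, ("b) over High CV risk patients only, and (c) over Very High CV risk patients only, identified in OM consultation".

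The text differs on the target group. The Abstract has high- and very-high-risk workers identified and the identified patients referred. The Introduction speaks of referring very-high-risk patients. Section 2.2 describes access to the consultation "through the systematic identification of very high CV risk patients in appointments from Occupational Health". Section 2.2.2 labels the whole set of referral criteria as very high risk.

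**The concern.** Two workers who both carry the label high risk are treated differently by Table 1 according to whether HDL was measured. Section 2.2.1.1 explains why SCORE is the fallback algorithm, but not why the qualifying category changes with it. Because endpoint 1 counts workers who meet Table 1, its value depends partly on laboratory availability.

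Endpoints 2 and 4(b) need a High category for every scored worker, and the article prints one only under SCORE. The article does not settle which of two readings applies:

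- **Reading A, High exists only under SCORE:** no worker assessed with SCORE2 can count as High in endpoint 2.
- **Reading B, High also exists under SCORE2** (as the Abstract's reference to ESC stratification suggests): the 4(b) denominator includes workers who meet no Table 1 criterion and whom the plan gives no reason to refer.

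These proportions are the main quantitative output on identification and referral, and Section 2.2.2 rests its precision statement on the share meeting the referral criteria.

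**Working it through.** **The plan's own figure.** Section 2.2.2 takes a prevalence of 15%, 1000 workers and 95% confidence. The half-width is 1.96 × √(0.15 × 0.85 / 1000) = 0.0221, which agrees with the stated 2.2%. Also 0.15 × 1000 = 150, the stated number of appointments. This arithmetic is not in question.

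**Assumed inputs.** The documents give none of the following, so all are illustrative, and the same prevalences are used under both algorithms:

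- v = share meeting a single-factor or very-high criterion, set to 15%
- g = share who are high only, set to 5%, 10% or 20%
- h = share of scored workers with HDL available, 0 to 100%
- s = share of SCORE2-high workers who also meet a single-factor criterion, set to 0 or 20%

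**Endpoint 1 = v + (1 − h) × g.** With v = 15%:

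| g | h = 100% | h = 50% | h = 0% | Full shift | Shift ÷ 2.21 |
|---|---|---|---|---|---|
| 5% | 15% | 17.5% | 20% | 5 points | 2.3 |
| 10% | 15% | 20% | 25% | 10 points | 4.5 |
| 20% | 15% | 25% | 35% | 20 points | 9.0 |

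If one rule covered both branches, this component of the shift would be zero.

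**Endpoint 2, with g = 10% and s = 0.** Under reading A it is (1 − h) × g: 10% at h = 0, 5% at h = 50%, 0% at h = 100%. Under reading B it is g = 10% at every h, so the Table 1 asymmetry does not move it.

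**Endpoint 4(b), highest attainable value with perfect referral.** Under reading A everyone in the denominator is SCORE-high and meets Table 1, so the ceiling is 100%. Under reading B the ceiling is (1 − h) + h × s:

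| h | s = 0 | s = 20% |
|---|---|---|
| 25% | 75% | 80% |
| 50% | 50% | 60% |
| 75% | 25% | 40% |
| 100% | 0% | 20% |

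The endpoint 2 problem thus arises only under A, and the 4(b) problem only under B.

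**The case against.** Several objections deserve weight.

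- **Endpoint 4(a) already measures referral fidelity with the right denominator.** This stands. A reader might infer that the plan as a whole would understate fidelity. It would not: 4(b) and 4(c) are descriptive breakdowns beside a sound 4(a).
- **The asymmetry may be a deliberate mapping between two scales.** The printed cut-offs differ, and the article does not say that high means the same risk on both. If SCORE-high was meant to match SCORE2-very-high, the endpoint 1 illustration would not apply as shown. But the article does not state this either, and workers at equal risk would then be High without HDL and Very High with it, so endpoints 2, 3, 4(b) and 4(c) would still divide by laboratory availability.
- **SCORE2-high workers are not shut out of referral.** A reader might infer that the plan never refers them. Table 1 refers any of them with a single markedly elevated factor, and the Abstract says identified patients are referred. The ceilings at s = 0 are therefore lower limits.
- **The inputs are assumed.** True. HDL-C is listed as a baseline variable in Table 2 and SCORE is called a fallback, so availability may be high. Nor do the documents support the inference that availability varies by company.
- **This is a descriptive pilot, and tabulation by algorithm can be left to an analysis plan.** In part this stands, and it lowers the severity. But Tables 1 and 3 are both fixed in this article and do not fit each other, which is a different matter from missing detail.

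**Conclusion.** The point holds and should be fixed, though it does not invalidate the study. Table 1 applies a different labelled threshold according to HDL availability, and the article contradicts itself on whether high-risk workers are among those targeted for referral. Endpoint 1 pools the two rules. With v = 15% and g = 10% it could lie anywhere from 15% to 25%, a range 4.5 times the stated margin. That size rests on assumed prevalences, taken as equal under both algorithms. The direction needs only that some workers are high risk without meeting another criterion and that the two high labels are comparable.

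For High, exactly one of two problems follows: endpoint 2 falls with HDL availability (reading A), or 4(b) has a ceiling below 100% whenever some SCORE2-high workers meet no Table 1 criterion (reading B). A reader might be tempted to claim both at once, but they rest on incompatible definitions. Endpoint 4(a) is free of the denominator problem, and the 2.2% margin is correctly computed.

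**What to change.** 1. Reconcile the two branches of Table 1 with each other and with the Abstract, the Introduction, Section 2.2 and Section 2.2.2. Which referral rule is right is for the clinicians.
2. Define High and Very High under each algorithm for endpoints 2 to 4.
3. Report endpoints 1 to 4 by algorithm used, that is, with and without HDL, alongside the pooled figure.
4. Restrict the 4(b) and 4(c) denominators to workers in that category who meet a Table 1 criterion, or state that 4(a) alone measures referral fidelity and that 4(b) and 4(c) are descriptive. For 4(c) the restriction changes nothing as long as Very High keeps the Table 1 bands.
5. Optionally, as a sensitivity analysis, compute SCORE in all workers aged 40 or more, so that endpoints 1 to 3 can also be shown on one metric.

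The cost is a text reconciliation, two definitions and a few table rows. No new data are needed: the algorithm follows from whether HDL was recorded at baseline, and Table 2 already collects birth year, sex, smoking, blood pressure and total cholesterol.

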#### Sample size

2.2.2

Based on prior publications (7, 12, 13), it was estimated that up to 15% of the studied population has at least 1 of the inclusion criteria for referral (very high cardiovascular risk), so there is the expectation to perform 150 cardiovascular risk appointments in the first 6 months of the project (6–7 appointments/week, divided into two weekly periods of 4 h).

In this sense, instead of a sample size calculation, a precision estimation was calculated: for a confidence interval of 95%, a prevalence of 15% and 1000 persons included, a margin of error of 2.2% is estimated. This precision-based estimate addresses the primary objective and the descriptive prevalence outcomes (secondary objectives 1, 2 and 5), for which the expected sample provides adequate precision. As a pilot implementation study, CARDIOGAP + is not powered to test a pre-specified hypothesis regarding the magnitude of risk-factor change; these analyses are exploratory and hypothesis-generating, intended to inform the design and sample size of a future, adequately powered evaluation.

The sample size may be adjusted to the participation of physicians from Occupational Health and participating companies, with ULSEDV having the capacity to accommodate more referrals.

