Atherosclerotic cardiovascular disease (ASCVD) incidence and mortality rates are declining in many countries in Europe, but it is still a major cause of morbidity and mortality (4). In fact, mortality data demonstrate that CVD remains the main cause of death in the European region. Furthermore, it is also important to acknowledge that there are important disparities across the different countries in the European region, as well as in the burden of CVD between men and women (5). Cardiovascular disease led to an annual toll of over 3.8 million deaths throughout Europe, comprising nearly 1.76 million deaths in men and exceeding 2 million deaths in women. This constituted 39% of all male deaths and 46% of all female deaths. In contrast, cancer, the second most prevalent cause of death in Europe, contributed to 24% of all male deaths and 20% of all female deaths (5). Although more women than men die from CVD in the region, higher age-standardized mortality and deaths in those aged <70 years demonstrate that CVD remains a greater burden among men in all countries. This observation substantiates the advocacy for alleviating the cardiovascular disease burden and mitigating disparities by instituting focused, evidence-driven interventions for both treatment and prevention across all Europe. In Portugal, atherosclerotic cardiovascular disease (ASCVD)-related costs amount to 1% of the Gross Domestic Product (6). In 2015, around 12% of the Portuguese population aged between 40 and 65 had a very high risk of developing a fatal cardiovascular event within the next 10 years. Thus, correctly identifying people with an elevated CV risk, at an early stage and the adoption of appropriate preventive strategies, is an important step to reduce CVD mortality in the Portuguese population (7).

While effective therapeutic strategies exist, much remains to be done in applying current knowledge more effectively and equitably in practice (3).

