### Strengths and limitations

2.4

CARDIOGAP + relies on a low-bureaucracy referral pathway designed for real-world adoption using mandatory occupational health infrastructure to screen a working-age population often missed by primary-care-based cardiovascular screening. In this context, three main limitations should be noted: Possible underestimation of true population-level risk (a “healthy worker effect”) due to restricting enrollment to currently employed individuals (since unemployed, informally employed, retired, and long-term sick-leave workers may carry a higher CV risk burden); Absence of power for a confirmatory test of 12-month risk-factor change (exploratory outcome); Barriers to hospital consultation adherence, which may be limited by shift workers’ difficulty attending hospital appointments, transportation constraints, low risk-perception among asymptomatic individuals, and gaps in OM-hospital communication

However, it should be noted that the low-bureaucracy design partially mitigates all these constraints and limitations, and their impact will be assessed empirically (secondary objectives 1, 2, 3, 7).

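### The 150 hospital appointments given as the expectation are the maximum from 1000 workers, reached only at the 15% upper bound with full referral and full attendance

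*Protocol article*

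**What the plan says.** Section 2.2.2 (Sample size) starts from a prevalence: "it was estimated that up to 15% of the studied population has at least 1 of the inclusion criteria for referral (very high cardiovascular risk"). From this it goes directly to a count: "so there is the expectation to perform 150 cardiovascular risk appointments in the first 6 months of the project", with a workload of "6–7 appointments/week, divided into two weekly periods of 4 h". The precision statement follows: "for a confidence interval of 95%, a prevalence of 15% and 1000 persons included, a margin of error of 2.2% is estimated". The section says that this precision serves the primary objective and secondary objectives 1, 2 and 5, and that the expected sample is adequate for them. It declares the risk-factor change analyses exploratory. It also allows the sample size to be adjusted to the participation of occupational physicians and companies, and says the hospital can take more referrals.

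Two other places bear on the count. In Table 3 (section 2.3.1), endpoint 4 is the proportion of qualifying workers who are referred, and endpoint 5 is the "percentage of individuals referred from OM consultations who participate in hospital CV risk consultations over all patients referred to hospital consultations". Section 2.4 gives, as one of three main limitations, "Barriers to hospital consultation adherence", citing shift work, transport, low perceived risk and communication gaps between occupational medicine and the hospital.

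**The concern.** Section 2.2.2 passes from workers who meet a criterion to appointments carried out, with no step for referral or attendance. It also uses a prevalence stated as an upper bound as if it were the expected value. The rest of the article does not assume perfect uptake: it lists reasons why workers may not attend and makes both rates outcomes of the study.

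At stake is the only size the article gives for the hospital cohort. The same patients supply attendance (endpoint 5), medication adherence (endpoint 6), 12-month change (endpoint 8) and lipoprotein(a) (endpoint 9). A reader will take 150 as the number to expect at T0. The same reader may also take the 2.2-point margin as covering secondary objective 2, the attendance rate, because the precision statement names that objective. The denominator of that rate is the referred workers and not the 1000 screened.

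**Working it through.** **Inputs from section 2.2.2:** 1000 persons; yield of at most 15%; 150 appointments; margin of error 2.2%; 6-7 appointments a week. **Not given anywhere in the article:** a planning value for the referral rate or the attendance rate.

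**Step 1. Reproduce the plan's figures.**
- Appointments = persons x yield x referral x attendance = 1000 x 0.15 x 1.00 x 1.00 = 150. This matches exactly. The article does not write out the multiplication, but these inputs give 150 only with both rates at 100%.
- Margin = 1.96 x sqrt(0.15 x 0.85 / 1000) = 0.0221, or 2.2 points. This matches.
- Workload: 150 / 26 weeks = 5.8 a week; 150 / 24 = 6.3; 150 / 22 = 6.8. This is consistent with 6-7 a week once some weeks are lost.

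**Step 2. Direction of the error.** The yield cannot exceed 15% on the stated bound, and neither rate can exceed 100%. Each factor is at its limit, so any departure lowers the product. For 1000 workers, 150 is the highest expected number. Chance could take an observed count above it; the point concerns the expectation.

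**Step 3. Size, on assumed rates.** Hold the yield at 15% and assume 80-100% referral and 60-80% attendance. These ranges are illustrative assumptions and do not come from the article.
- Low end: 150 x 0.80 x 0.60 = 72.
- High end: 150 x 1.00 x 0.80 = 120.

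**Step 4. Precision of the attendance proportion.** The denominator is the number referred: at most 150 at full referral, or 150 x 0.80 = 120 at 80% referral. With margin = 1.96 x sqrt(p(1 - p) / n):

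| Assumed attendance | n = 150 referred | n = 120 referred |
|---|---|---|
| 80% | 1.96 x sqrt(0.16/150) = 6.4 points | 1.96 x sqrt(0.16/120) = 7.2 points |
| 60% | 1.96 x sqrt(0.24/150) = 7.8 points | 1.96 x sqrt(0.24/120) = 8.8 points |

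At an assumed 80%, the best case is about 6.4 points, roughly three times the quoted 2.2 (6.4 / 2.2 = 2.9). The 2.2 remains correct for a proportion of all 1000 workers.

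**The case against.** The strongest defence is that nothing is miscalculated. The count, the margin and the weekly workload all reproduce. Using full uptake for planning does not conflict with measuring uptake as an endpoint, and the attendance barriers are disclosed. The study is an unpowered pilot, no success threshold is tied to 150, and no 12-month cohort size is claimed. Most of this stands. The fault lies in calling a maximum the expectation, and no analysis fails because of it.

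Two parts of the defence do not remove the point. The adjustment clause covers participation by physicians and companies, not workers who are referred and do not attend. Nor can 150 be read as a capacity limit, since the section says that the hospital can accommodate more.

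A reader might infer more: that 15% is itself refuted by the Introduction, which reports that "around 12% of the Portuguese population aged between 40 and 65 had a very high risk of developing a fatal cardiovascular event", whereas the study enrols workers aged 18 to 70 and the risk scores apply only from age 40. The documents do not support that. Table 1 also admits workers on markedly raised cholesterol, blood pressure or reduced kidney function, with no age floor, and admits high as well as very high risk under SCORE. The 15% rests on three references, and what the other two report is not shown. The possible healthy-worker effect in section 2.4 concerns underestimation of population risk and does not say that 15% is too high for these workers. The age structure of the workforce is not given, so no lower yield can be derived. A reader might also infer that fewer than 150 consultations would count as an implementation failure, or that the clinic slots should be cut. The endpoints are proportions over actual denominators, and nothing in the article supports either inference.

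**Conclusion.** The point holds in a limited form. As worded, 150 is the maximum expected from 1000 workers, conditional on a true yield of 15%, full referral and full attendance. The article's own limitation on attendance, together with its treatment of both rates as unknown, means it cannot also be the expected T0 cohort. That conclusion needs no outside figure.

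The size of the shortfall does rest on assumptions. The range of 72 to 120 follows from the assumed rates and would move with them. The margin of about 6.4 points for attendance assumes 150 referred and 80% attending. The 2.2-point margin for proportions of all 1000 workers is unaffected. The consequence is modest, since the 12-month analyses are declared exploratory, but the hospital cohort should be described correctly and the adequate-precision statement should not extend the 2.2 points to secondary objective 2.

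**What to change.** In section 2.2.2, keep the 1000 workers and change the wording as follows.
- Call 150 the maximum under a 15% yield with full referral and attendance.
- State the referral and attendance rates assumed for planning.
- Give the expected T0 number as a range labelled as an assumption. For example, a 15% yield with 80-100% referral and 60-80% attendance gives 72 to 120; the investigators should substitute their own rates if they have better ones.
- Use that range when describing the cohort at T0 and T12. The T12 number will be no larger than the T0 number.
- Limit the 2.2-point margin to proportions of all 1000 workers, and give a separate margin for attendance based on the number referred (about 6.4 points at 150 referred and an assumed 80%).

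This costs a few sentences. It adds no patients or visits and changes no endpoint or analysis. The stated cohort size and the precision for attendance become less favourable.

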#### Primary objective

2.1.1

To implement a streamlined process to promote access to a CV risk hospital consultation, through the systematic identification of individuals with elevated CV risk in OM consultations carried out in industrial/manufacturing companies’ workers in the municipality of São João da Madeira.

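### The 2.2-point margin in section 2.2.2 is a margin for the prevalence of the referral criteria, not for the access, referral and attendance objectives it is said to cover

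*Protocol article*

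**What the plan says.** Section 2.1.1 of the protocol article gives the primary objective: "To implement a streamlined process to promote access to a CV risk hospital consultation", by way of systematic identification of workers at elevated risk in occupational medicine (OM) consultations. Secondary objectives 1 and 2 (section 2.1.2) are the rate of referral among identified workers and the rate of hospital consultations that took place after referral.

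Section 2.2.2 replaces a sample size calculation with a precision estimate: "for a confidence interval of 95%, a prevalence of 15% and 1000 persons included, a margin of error of 2.2% is estimated". The 15% is defined just before: "up to 15% of the studied population has at least 1 of the inclusion criteria for referral". From it the section derives a workload: "there is the expectation to perform 150 cardiovascular risk appointments in the first 6 months of the project". It then states what the margin is for: "This precision-based estimate addresses the primary objective and the descriptive prevalence outcomes". It lists secondary objectives 1, 2 and 5 as those outcomes and judges the precision adequate for them.

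Table 3 uses three different denominators:

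- Endpoint 1 is the "percentage of patients who meet the follow-up criteria for CV risk hospital consultation over all patients attending OM consultations".
- Endpoint 4(a) is the proportion referred, among patients who meet those criteria.
- Endpoint 5 is the proportion who take part in the hospital consultation, among those referred.

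Table 3 labels no endpoint as primary.

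**The concern.** A margin of error belongs to one proportion on one denominator. The 2.2 points belong to the share of 1000 OM attendees who meet a referral criterion. Whether those workers are then referred, and whether they attend, does not enter that share. Section 2.2.2 nevertheless extends the margin to an objective about access and to two rates whose denominators are a fraction of the 1000.

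A reader of section 2.2.2 will expect referral and attendance to be known to within about 2 points. The results will carry intervals roughly three times as wide or more. Section 2.4 names barriers to attendance as a main limitation and says their impact will be assessed through secondary objectives 1, 2, 3 and 7, so these are the rates on which an honest statement of precision matters most.

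The two steps also need to be read together. As an illustration, 90% attendance after 40% referral is 0.90 × 0.40 = 36% access. Neither endpoint 4(a) nor endpoint 5 shows that figure alone, and no planned endpoint reports it with an interval.

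**Working it through.** **Inputs.** From section 2.2.2: 95% confidence, prevalence 15% (an upper figure), n = 1000. From Table 3: the denominators of endpoints 1, 4(a) and 5. The article gives no referral or attendance rate, so rates of 50% to 90% are assumed.

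**Formula.** Half-width = 1.96 × √(p(1 − p)/n), simple binomial.

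**Step 1: the plan's own figure.** 1.96 × √(0.15 × 0.85/1000) = 0.0221, or 2.2 points. It reproduces. A Wilson interval gives 12.9% to 17.3% and a Clopper-Pearson interval 12.8% to 17.4%, so the choice of method does not matter.

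**Step 2: the denominator for referral.** Workers meeting the criteria: 0.15 × 1000 = 150. The 150 expected appointments are this same product, so that expectation takes every criteria-positive worker to be referred and to attend.

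**Step 3: half-widths for referral at n = 150** (and for attendance, if all 150 are referred).

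| Assumed rate | Calculation | Half-width (points) |
|---|---|---|
| 50% | 1.96 × √(0.25/150) | 8.0 |
| 70% | 1.96 × √(0.21/150) | 7.3 |
| 80% | 1.96 × √(0.16/150) | 6.4 |
| 90% | 1.96 × √(0.09/150) | 4.8 |

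Between 50% and 80% this is 8.0/2.2 = 3.6 down to 6.4/2.2 = 2.9 times the stated margin.

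**Step 4: smaller denominators.** If 70% of the 150 are referred, attendance rests on n = 105:

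- at 50%: 1.96 × √(0.25/105) = 9.6 points
- at 70%: 1.96 × √(0.21/105) = 8.8 points
- at 80%: 1.96 × √(0.16/105) = 7.7 points

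If prevalence is 10% instead of 15%, referral rests on n = 100, and at 50% the half-width is 1.96 × √(0.25/100) = 9.8 points.

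**Step 5: end-to-end access (attended among criteria-positive, n = 150).**

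| Referral | Attendance | Access | Consultations held | Half-width (points) |
|---|---|---|---|---|
| 50% | 50% | 25% | 37.5 | 6.9 |
| 70% | 70% | 49% | 73.5 | 8.0 |
| 80% | 80% | 64% | 96 | 7.7 |

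In every row endpoint 1 stays at 15% ± 2.2 points, because neither referral nor attendance enters it.

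**Step 6: what 2.2 points would take.** n = 1.96² × p(1 − p)/0.022² gives about 1,985 criteria-positive workers at p = 50% and 1,270 at 80%. Divided by 0.15, that is about 13,230 and 8,470 workers screened, against 1000 planned.

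**The case against.** A reader might infer that the study has no figure that could show whether the process worked, and that its primary objective would look fulfilled even if nobody reached the hospital. The documents do not support that, for four reasons.

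- Endpoints 4(a) and 5 are planned, and a failed pathway would show in them. Section 2.1 also names participation in the hospital consultation as a means of evaluating the intervention. If all referred workers meet the criteria, as section 2.2.1.1 intends, the end-to-end proportion is simply the product of the two.
- The 150 expected appointments are a second figure in section 2.2.2, and the number actually held would fall short of it if workers did not attend.
- Table 3 names no primary endpoint, so endpoint 1 is nowhere declared the measure of success. Section 2.2 has the enrolment phase serve the primary objective and secondary objectives 1, 2 and 5 together.
- The primary objective works through systematic identification, and endpoint 1 does describe the yield of that step.

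One can add that this is a single-arm descriptive pilot with no success threshold, and that the article condenses a fuller protocol which may name a primary endpoint.

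All of this stands, and it limits the point. It does not rescue the precision statement, which the article makes explicitly and which assigns a margin on n = 1000 to rates measured on about 150 workers or fewer. The 150 appointments are a workload expectation, not a precision for referral or attendance.

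**Conclusion.** The point holds in a narrow form. The 2.2-point margin is correct for a 15% prevalence on 1000 workers. It may stand for endpoints 1 to 3 and for secondary objective 5, exactly at 15% and approximately near it. It is wrong for referral and attendance, and it says nothing about the access part of the primary objective. For those, the half-width is about 6 to 8 points at rates of 50% to 80% with 150 workers, and close to 10 points at a rate of 50% with about 100.

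This rests on assumed referral and attendance rates, on 15% being the plan's upper prevalence figure, and on simple binomial variation. A margin of 6 to 8 points is still informative for a pilot, so the design is not in question. What needs correcting is the stated precision. The lack of a reported end-to-end proportion is a lesser gap, because its components are already planned.

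**What to change.** In section 2.2.2, limit the 2.2-point margin to the prevalence outcomes. State separately that referral and attendance will be estimated on their own denominators, with a 95% half-width of about 6 to 8 points at n = 150 for rates of 50% to 80%, and wider if fewer workers meet the criteria or are referred.

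In Table 3, add as the measure of the access objective the proportion of enrolled workers meeting the Table 1 criteria who had a T0 consultation, with a 95% CI. State the date by which a T0 visit must have been held to count. Keep endpoints 4 and 5 as the component steps and endpoints 1 to 3 as descriptive prevalence.

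The cost is a change of wording in two places. The Table 1 inputs, the OM destination item and the visit dates are already recorded, so no new data are needed and no clinical procedure changes. The downside is that the precision stated for access is less favourable than 2.2 points.
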